## Abstract

**Background:**

Burnout has received limited attention in treatment programs, despite high prevalence among health professionals and the threat burnout places upon the mental health and the long-term sustainability of the Australian healthcare system. As part of The Essential Network (TEN), a blended care mental health support service for Australian health professionals, we developed Navigating Burnout – a digital cognitive-behavioural therapy program for health professional burnout. This three-arm randomised-controlled trial (RCT) will examine the effectiveness, acceptability, and cost-effectiveness of Navigating Burnout in both blended care and digital formats in reducing burnout among doctors.

**Methods:**

Doctors (n = 207) with burnout will be randomised to (1) a blended version of Navigating Burnout combining digital resources with five fortnightly telehealth sessions with a clinical psychologist, (2) a digital-only version of Navigating Burnout, or (3) self-care psychoeducation as an active attention control. Burnout, psychosocial wellbeing, workforce engagement and attrition, and service acceptability will be measured at baseline, post-treatment, and 3 months post-treatment.

**Results:**

At 3 months post-treatment, we hypothesise reductions in burnout across both treatment arms, with the strongest effect in the blended care arm. Similar trends are expected for psychosocial and occupational outcomes. High service acceptability across both blended care and digital-only versions of Navigating Burnout is also anticipated.

**Conclusions:**

With this evidence, Navigating Burnout may be incorporated into TEN's person-to-person components. Further, by demonstrating the effectiveness of blended care for burnout, Navigating Burnout may provide a crucially needed service for Australian doctors and replicable model of care for other organisations and support services.

## Introduction

1

The healthcare industry places significant demands on doctors, including protracted working hours in highly stressful conditions [1] alongside understaffing [2] and a lack of job control [3]. The COVID-19 pandemic intensified these pressures, leading to moderate-to-severe burnout in approximately 50% of health professionals, with doctors more likely to experience physical and emotional exhaustion than their non-medical colleagues [4].

Burnout is a work-related syndrome characterised by emotional exhaustion, disengagement from work, and a reduced sense of accomplishment [5]. Burnout is not currently listed in the Diagnostic and Statistical Manual of Mental Disorders as a diagnosable mental disorder, and there is an ongoing debate as to whether burnout constitutes a type of depression or a unique condition [6,7]. Nevertheless, the syndromic characteristics of burnout have been shown to jeopardise doctors’ mental health [8], reduce professionalism in healthcare [9], increase workplace attrition [10], and compromise patient safety [9,11]. Indeed, a recent meta-analysis found that high levels of burnout among doctors was associated with a doubling of patient safety incidents, as well as a threefold increase in turnover intention [9]. These outcomes pose significant risks to the effectiveness and sustainability of the healthcare system for the public benefit.

Despite the wide prevalence and known risks of burnout in doctors, almost no established programs exist to help address burnout in doctors or health professionals more broadly. While there is a growing local [12] and international [5] consensus that burnout in medicine has systemic causes that require systemic interventions, most current research focuses on supporting individuals. Several meta-analyses have found mixed support for the efficacy of the limited available interventions in addressing burnout, in part due to high heterogeneity in definition and measurement of burnout, intervention content, and quality of trial design [[13], [14], [15]]. Despite this heterogeneity, several studies have found support for web-based cognitive-behavioural therapy (CBT) as a promising and scalable treatment option [16,17].

In 2020, the Black Dog Institute (BDI) launched The Essential Network (TEN), funded as part of the Australian Government's response to COVID-19 [18]. TEN is a blended care mental health support service designed by-and-for health professionals that combines digital and person-to-person care. TEN provides healthcare professionals with access to an online digital gateway which features tools such as a digital mental health check-up and evidence-based programs and resources tailored to the needs of health professionals. Digital services are complemented by connection to person-to-person care with up to with up to five free telehealth sessions with a clinical psychologist or psychiatrist through the BDI Clinical Service.

Although evaluations found that the initial TEN program provided effective support for psychological stress management, the initial program did not adequately address the more prominent complaint of burnout [19,20]. Based on this insight, as well as the virtual absence of tailored treatment programs for burnout in health professionals, we developed a first-of-kind digital program called “Navigating Burnout” to expand the TEN program. Navigating Burnout is a novel self-guided digital CBT and acceptance and commitment therapy (ACT) program tailored to the needs of health professionals experiencing, or at risk of, burnout. Upon successful evaluation, Navigating Burnout will be fully integrated into the TEN program.

This randomised-controlled trial (RCT) aims to establish evidence on the effectiveness, acceptability, and cost-effectiveness of Navigating Burnout across blended and self-guided modes of delivery. Such evidence will inform the integration of Navigating Burnout into TEN's person-to-person care to better support health professionals experiencing burnout, as well as highlight the efficacy of Navigating Burnout as a scalable digital program to mitigate burnout among health professionals.

## Methods

2

### Trial design

2.1

We will conduct a three-arm RCT to compare the effectiveness, acceptability, and cost-effectiveness of Navigating Burnout in reducing burnout among doctors across three delivery modalities.

Medical doctors (n = 207) will be randomly allocated to receive either [1] a blended version of the program combining the digital Navigating Burnout resources with five fortnightly telehealth sessions with a clinical psychologist [2]; a digital-only, self-guided version of the Navigating Burnout program; or [3] an active attention control where participants will be provided with digital self-care psychoeducation via email each fortnight. Across all conditions the treatment phase across will last 10 weeks.

We will measure self-reported burnout, psychosocial wellbeing, workforce engagement, and workforce attrition intentions before treatment, immediately after treatment, and 3 months after completing treatment (see Fig. 1 for trial design). This design will enable us to examine the effectiveness and acceptability of blended care Navigating Burnout compared to self-guided Navigating Burnout, as well as to examine the effectiveness of self-guided Navigating Burnout relative to an appropriate control.

**Fig. 1 fig1:**
[figure not shown]
Schematic diagram of trial design. Figure legend: Oldenburg Burnout Inventory (OLI-16), Depression Anxiety Stress Scale (DASS-21), Work and Social Adjustment Scale (WSAS), World Health Organisation Health and Work Performance Questionnaire (WHO-HPQ), Turnover Intention Scale-6 (TIS-6), and Client Satisfaction Questionnaire (CSQ-8).

### Participants

2.2

Individuals will be eligible to participate in the trial if they satisfy all of the following criteria.•registered doctor currently practising in Australia;•able to read and speak English fluently;•current experience of self-reported burnout;•able to access the internet in a private location on a device suitable for viewing websites and attending telehealth consultations; and•able to attend telehealth consultations during Monday to Friday business hours (9.00–17.00).

Individuals will be excluded from trial participation if they satisfy any one or more of the following criteria.•current diagnosis of severe mental illness that requires more specialist support (e.g., bipolar disorder, schizophrenia, etc.);•current engagement with person-to-person psychological therapy (e.g. cognitive-behavioural therapy);•DASS-21 symptom scores in the Severe or Extremely Severe ranges for anxiety or depression during screening; or•report suicidal ideation or problematic alcohol or drug use during screening.

### Interventions

2.3

Navigating Burnout is a digital psychotherapeutic program that includes intervention components derived from evidence-based cognitive-behavioural and acceptance and commitment therapies that are delivered across seven topics [1]: understanding burnout [2]; increasing social connections [3]; managing unrealistic expectations [4]; setting limits [5]; valued living [6]; self-care; and [7] a module for managers detailing evidence-based strategies for improving workplace mental health (see Fig. 2). Each topic contains lived experience videos, behavioural strategies, and CBT worksheets.

**Fig. 2 fig2:**
[figure not shown]
Example screenshot from Navigating Burnout.

In the blended care arm, a clinical psychologist from the BDI Clinical Service will work through the Navigating Burnout content with participants over 10 weeks in five fortnightly 1-hour consultations. Clinical psychologists will follow a treatment manual mirroring the content of Navigating Burnout, with guidance on integrating digital content into session activities. Session 1 covers understanding burnout and self-care, session 2 covers unrealistic expectations, session 3 covers setting limits, session 4 covers valued living, and session 5 covers increasing social connections and information for managers. Session 1 is fixed and the same for all participants, whereas sessions 2–5 occur in an order determined by the participant and their clinical psychologist. Clinical psychologists will be offered a training program comprising [1]: a comprehensive treatment manual summarising the study protocol, the digital content, and session plans with suggested approaches to delivering the program's CBT strategies [2]; a 90-min protocol training session delivered by PB covering the design and purpose of the study, how to use the training manual, how to embed the digital content in a standard telehealth consultation, and roleplays of case examples; and [3] optional monthly 60-min clinical supervision sessions with PB. Clinicians will have discretion to tailor consultations to participant needs as long as (a) the clinical focus remains burnout; and (b) the program content is delivered in full across the five consultations. Participants will also have independent access to the digital version of Navigating Burnout over the 10 weeks between consultations and be directed by their clinical psychologist to specific components of the program in order to support awareness and management of burnout. During the 10-week treatment period, clinical psychologists providing care in the blended arm will provide immediate risk assessment and intervention for any participant expressing intent to self-harm or suicide and report any concerns related to suicide or self-harm attempts to PB.

In the self-guided arm, participants will be emailed a link to Navigating Burnout to engage with independently over 10 weeks. While participants will have access to the entirety of Navigating Burnout from onset, progress will be supported by fortnightly structured reminders that encourage participants to continue working through the course.

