### Sample size

2.12

We will enrol 207 participants to complete the trial. This sample size is sufficient to examine the primary outcome using repeated measures ANOVA of whether the blended care version of the Navigating Burnout program leads to significantly lower burnout between baseline and 3 months post-intervention compared to self-guided treatment based on a power analysis (α = .05 and power = 0.80) using a conservative medium effect size of f = 0.25 between groups estimating a sample size of 53 per arm (WebPower). As there is limited literature on the effect of blended care treatments for burnout relative to self-guided digital psychotherapeutic programs, a medium effect size of f = 0.25 was chosen as a minimum clinically meaningful effect [28]. Accounting for a conservative estimate of 30% attrition based on previous research health professionals [19], 69 participants are required in each arm leading to a total sample size of 207.

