### Statistical methods

2.13

Study analyses will follow an intention-to-treat analysis plan using multiple imputation to account for missing data. To understand baseline variation and ensure experimental rigor, baseline scores on all psychosocial and occupational outcomes will be checked for between arm consistency using one-way analysis of variances (ANOVAs).

For the primary outcome (changes in OLBI burnout scores), between group variations (i.e., reductions in burnout between arms) will be examined using a 3 (blended, self-guided, active attention control) x 2 (baseline, 3 months post-treatment) mixed model ANCOVA controlling for gender, age, profession, and regionality and explored with pairwise comparisons. Identically formatted mixed model ANCOVAs will be used to analyse the secondary aims and outcomes of between arm and baseline to post-treatment and 3-month post-treatment differences in DASS (anxiety and depression), WSAS (psychosocial functioning), WHO-HPQ (workplace participation), and TIS-6 (attrition intention). The secondary aim and outcomes of comparing service acceptability between arms will be analysed using one-way ANOVAs.

If primary outcome data (i.e. OLBI at 3 months post-treatment) is unavailable for more than 5% of participants from the intention-to-treat population then exploratory and sensitivity analyses will be conducted. The following exploratory analyses of missing primary outcome data will be conducted to inform missingness categorisation and missing data handling: comparing proportion of attrition between arms, reasons for withdrawal, and baseline characteristics between those with and without the primary outcome. Best-worst and worst-best case sensitivity analyses will also be conducted alongside sensitivity analyses using last observation carried forward. Based on the results of these exploratory and sensitivity analyses, either complete case analysis or multiple imputation with 100 imputed data sets of the primary outcome will be conducted.

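### The primary model ignores possible clustering by psychologist in the blended arm, so if the therapist ICC is above zero, both blended-arm comparisons have standard errors that are too small

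*Protocol article*

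**What the plan says.** Section 2.3 of the protocol article describes delivery in the blended arm: "a clinical psychologist from the BDI Clinical Service will work through the Navigating Burnout content with participants over 10 weeks", in five fortnightly one-hour consultations. The psychologists follow a manual, but "Clinicians will have discretion to tailor consultations to participant needs", provided that burnout stays the focus and all content is delivered. Training is offered and monthly supervision is optional. Section 2.8 expects that some first consultations will be delayed because clinicians have no free capacity.

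The other arms involve no therapist. Self-guided participants work alone from an emailed link with reminders (2.3), and controls receive fortnightly emails (2.4).

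Section 2.13 sets the primary analysis as a 3 (arm) x 2 (baseline, 3 months post-treatment) "mixed model ANCOVA controlling for gender, age, profession, and regionality and explored with pairwise comparisons". Section 2.12 sizes the trial on blended vs self-guided: "a medium effect size of f = 0.25 was chosen as a minimum clinically meaningful effect", which leads to 53 per arm and, after an allowance for attrition, "69 participants are required in each arm leading to a total sample size of 207". Neither section mentions the psychologist, an ICC or a design effect.

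**The concern.** Participants are randomised individually, but in one arm the treatment comes from a limited group of people. Participants who share a psychologist may have more similar outcomes than participants who do not. The design is then partially nested: clustered in the blended arm and independent in the other two. A between-within ANCOVA recognises only the correlation between two measurements on the same participant. It therefore counts the blended participants as fully independent and gives the blended mean more precision than it has.

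This affects the question the trial is sized to answer. Section 5 makes adoption of the blended program within TEN conditional on these results, so an interval that is too narrow for blended vs self-guided would matter in practice.

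**Working it through.** **Inputs from the protocol.** Alpha 0.05, power 0.80, f = 0.25, 53 per arm before attrition and 69 per arm enrolled (2.12); 1:1:1 individual randomisation (2.6); therapist in the blended arm only (2.3, 2.4); no clinician term (2.13).

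**Inputs assumed, because the documents do not give them.** Number of psychologists k = 4 to 12, equal caseloads, and therapist ICC 0.01 to 0.10 for the change in OLBI.

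**1. Reproduce the plan's figure.** Use a noncentral F test for three groups (numerator df 2) with noncentrality N x f². Power first reaches 0.80 at N = 158, where the noncentrality is 158 x 0.0625 = 9.875. That is 53 per arm, and power at 159 is 0.805. The stated 53 therefore follows from independent participants, with no allowance for clustering.

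**2. Effect of clustering in one arm.**
- Caseload: m = n/k
- Design effect in the blended arm: DE = 1 + (m − 1) x ICC
- True SE divided by model SE, for blended vs either other arm: R = √((DE + 1)/2)
- Shortfall of the model SE: 1 − 1/R
- Actual two-sided type I error: 2 x (1 − Φ(1.96/R))

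**3. One case in full: 53 per arm, 6 psychologists, ICC 0.05.** m = 53/6 = 8.83. DE = 1 + 7.83 x 0.05 = 1.392. R = √(2.392/2) = 1.094. The model SE is 1 − 1/1.094 = 8.6% too small. Type I error is 2 x (1 − Φ(1.96/1.094)) = 0.073. The blended arm carries the information of 53/1.392 = 38 independent participants.

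**4. Range with 53 analysed per arm.** Each cell gives DE; SE shortfall; type I error.

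| Psychologists | ICC 0.01 | ICC 0.05 | ICC 0.10 |
|---|---|---|---|
| 4 | 1.123; 2.9%; 0.0571 | 1.613; 12.5%; 0.0864 | 2.225; 21.3%; 0.1227 |
| 6 | 1.078; 1.9%; 0.0545 | 1.392; 8.6%; 0.0731 | 1.783; 15.2%; 0.0966 |
| 8 | 1.056; 1.4%; 0.0532 | 1.281; 6.4%; 0.0665 | 1.562; 11.7%; 0.0834 |
| 12 | 1.034; 0.8%; 0.0520 | 1.171; 4.0%; 0.0599 | 1.342; 7.6%; 0.0701 |

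**5. All 69 analysed after imputation.** Caseloads are larger. The SE shortfall is 1.2% to 25.7% and type I error 0.0527 to 0.1454. With 6 psychologists and ICC 0.05 they are 11.0% and 0.0811.

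**6. Check by simulation.** A three-arm analysis with pooled error was simulated with 40,000 runs per setting and 53 per arm.

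| Setting | Blended vs self-guided | Blended vs control | Self-guided vs control |
|---|---|---|---|
| 6 psychologists, ICC 0.05 | 0.073 | 0.072 | 0.050 |
| 4 psychologists, ICC 0.10 | 0.123 | 0.125 | 0.054 |

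At ICC = 0, type I error stays at about 0.05 for all three contrasts.

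**7. Power with a correct SE.** Power = Φ(0.5/√((DE + 1)/n) − 1.96), where d = 0.5 corresponds to f = 0.25 in a two-group contrast. With 53 per arm this is 0.730 under independence (DE = 1) and 0.653 at DE = 1.392. Over the whole range it is 0.723 to 0.527. The starting value is below 0.80 because 53 per arm is the three-group figure, which is a separate matter.

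**The case against.** **The analysis plan may deal with it.** This is a journal article, and random effects and degrees of freedom are often left to the analysis plan. That would be decisive if section 2.13 were silent. But it states the primary model and lists its covariates, and a clinician term would change that model. The point concerns what is stated, although an unseen plan may already correct it.

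**Delivery is standardised.** There is a manual, a fixed first session, a rule that all content be delivered, a training session and a fidelity survey after every consultation (2.3, 2.11), and all blended participants use the same digital material. This stands as a reason to expect a modest ICC. It does not rule out therapist variance: the order of sessions 2 to 5 is flexible, tailoring is allowed, supervision is optional, and the survey anticipates that the suggested structure may not be followed at all.

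**Shared caseloads are not stated.** This is correct. They are inferred from 69 participants, one clinical service and the remark about clinicians at capacity. The inference is strong, but the degree of sharing, on which the size depends, is unknown.

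**The remedy may be unstable with few psychologists.** This also stands, and the fix allows for it.

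**Conclusion.** The point holds in conditional form. If the therapist ICC is above zero and psychologists share caseloads, the model as written understates uncertainty for both blended contrasts and leaves self-guided vs control essentially untouched. Under the assumed ranges the effect runs from negligible (type I error 5.2%) to material (12.3%), with 7.3% at 6 psychologists and ICC 0.05. It is greater if all 69 per arm are analysed. The upper end needs the fewest psychologists and the highest ICC together.

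A reader might infer that the standard errors are certain to be too small. The documents do not support that: they give no ICC, and at zero there is no bias. Nor should the ratio R be read as the shortfall. With R = 1.27 the true SE is 27% larger than the model's, but the model's SE is 21% too small.

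The change should be made, because it is cheap and concerns the comparison that sizes the trial. It does not show the trial to be invalid.

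**What to change.** Record the treating psychologist for each blended participant; the survey completed after each session (2.11) is a convenient place. In section 2.13, add a psychologist random effect that applies to the blended arm only, with each participant in the other arms as their own cluster (a partially nested mixed model). Use Kenward-Roger or Satterthwaite degrees of freedom and report the estimated ICC. The effect should act on the follow-up score or on change: baseline is collected before randomisation, and an effect common to both time points would cancel from the arm-by-time contrast.

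If too few psychologists take part for stable estimation, report this model as a prespecified sensitivity analysis, with the number of psychologists and their caseloads.

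The cost is one variable, one model term and slightly wider intervals for the two blended contrasts: about 9% wider with 6 psychologists and ICC 0.05 (R = 1.094), before the adjustment to the degrees of freedom. Self-guided vs control is essentially unchanged.

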### Control

2.4

In the control condition, participants will receive an active attention control comprising of fortnightly emails containing links to generic digital self-care psychoeducation materials. The digital self-care psychoeducation was based on the self-care component of Navigating Burnout, expanded to include additional generic self-care content. The email cadence was chosen to align with the fortnightly structure of reminders in the self-guided arm (i.e., emails will provide participants with information to work through fortnightly). While self-care is included in Navigating Burnout for the purpose of maintaining or improving general mental well-being, previous research has found that self-care alone does not produce a measurable impact on burnout outcomes [21]. Thus, self-care materials were chosen as a suitable attention control that is not expected to treat burnout.

